#### Study plan

As explained in the SPIRIT table (Table 1), all patients with gastrointestinal tumors are routinely screened for CRF with the Hornheider’s questionnaire. If CRF is detected (severity grade > 4 and a disability score > 5) and the patient could be eligible to participate (inclusion/exclusion criteria), he/she is informed about the study and receives a study flyer. If the patient wants to participate, he/she gets an appointment at the outpatient clinic of the Neurosurgical Department of the University Medical Center Knappschaftskrankenhaus Bochum.

### Visit 0

At this time, the patient will give his informed consent. Then he/she receives the stimulator and is instructed how to use it. He/she is also asked to install the manufacturer’s app on the smartphone (“tvns patient” on Google Play® and Apple App Store®). The stimulator is paired with the smartphone app, logs the stimulation intensity and duration for each day, and reminds the patient to stimulate. The data of the app can only be read by the patient and will be documented by the physician at the end of the study, together with the patient.

Personal data like age, sex, height, and weight will be recorded. Also, it will be noted whether the patient is still under radio- or chemotherapy. The three questionnaires are filled out, and the patient is discharged. After 1 week, he/she will be called by our study nurse and asked if he/she has any questions or problems with the stimulation. The last visit will be 4 weeks later. The patients are advised to contact the principal investigator whenever a side effects occur.

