**Methods:**

Thirty adult patients with gastrointestinal tumors during or after treatment, relevant CRF (Hornheide questionnaire) and life expectancy > 1 year, are enrolled. Patients are randomized to treatment or sham arm and be informed that they will either feel the stimulation or not. Treatment group will receive left-sided tragus above-threshold stimulation with 25 Hz, 250 µs pulse width, and 28-s/32-s on/off paradigm for 4 h throughout the day for 4 weeks. Sham group will receive no stimulation via a nonfunctional electrode. A daily stimulation protocol with time and average intensity is automatically created by a smartphone app connected to the stimulator via Bluetooth®. Multidimensional Fatigue Inventory-20, Short-Form 36 and Beck Depression Inventory questionnaires will be filled out before and after 4 weeks of stimulation.

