### Patients

In accordance with the NCCN guidelines, all admitted patients of the Department of Haematology, Oncology and Palliative Medicine at the St. Josef-Hospital Bochum, who suffer from malignant gastrointestinal tumors, are routinely screened with a short CRF screening test (Hornheide’s questionnaire). If — before the initiation of an adjuvant therapy, a severity grade > 4 and a disability score > 5 are detected, eligible patients will be asked to participate in the study.

GDPR-compliant data collection will be pseudonymized in the eCRF of the university’s REDCap® system. The patients are automatically randomized by REDCap® into the stimulation or sham group (*n* = 15 each). Since the patients in the sham group will also be instructed in the use of the stimulator (which describes a tingling sensation of the stimulation in the ear), sham patients are told that they will receive a stimulation below the perception threshold. Since the rule “the more, the better” is not necessarily applicable in vagal nerve stimulation and a stimulation below the perception threshold could theoretically be effective, this procedure seems to be justifiable.

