### Stimulation group

The device we use in this trial is the tVNS-L system manufactured by tVNS GmbH, Erlangen, Germany. It has a CE certificate for left-sided transcutaneous auricular vagal nerve stimulation with a fixed frequency of 25 Hz, pulse width of 250 µs, and 28-s on/32-s off protocol, and a variable stimulation intensity. It is an over-the-counter available system which can be bought in the manufacturer’s online shop. The stimulation will be performed at the tragus of the left ear in accordance with the CE certificate. The stimulation intensity is adjusted by the patient just above the perception threshold, until a light tingling is felt at the electrode. The stimulation shall be done for in total 4 h throughout the day, but not necessarily for 4 consecutive hours.

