### Sham group

For stimulation in the sham group, the manufacturer offers a non-connected fake electrode which looks identical to the real electrode. Resistors within the electrode report a sufficient impedance to the stimulator so the control-LED of tVNS-L will always show good contact to the skin. The patient will be told that he/she is either in the group where he can feel the stimulation or in the group where the stimulation is below the threshold. The patients will therefore be blinded, the doctors won’t.

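### As narrated, Visit 0 takes the baseline questionnaires after the arm-specific device is handed over, and nothing shown fixes them before allocation is revealed

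*Protocol article*

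**What the plan says.** The only account shown of the order of events at the first visit is in the Study plan, under Visit 0. It opens with "At this time, the patient will give his informed consent" and continues "Then he/she receives the stimulator and is instructed how to use it". App installation and pairing come next, then personal data and current therapy, and finally "The three questionnaires are filled out, and the patient is discharged".

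Four other places bear on the point:

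- **Abstract, Methods:** the "questionnaires will be filled out before and after 4 weeks of stimulation". This sets the baseline before the treatment period but says nothing about allocation or hand-over.
- **Patients:** "The patients are automatically randomized by REDCap® into the stimulation or sham group", 15 per arm, with no time point within the visit. The same section says that, because the device instruction describes a tingling sensation, "sham patients are told that they will receive a stimulation below the perception threshold".
- **Stimulation group:** "The stimulation intensity is adjusted by the patient just above the perception threshold", with tingling as the cue.
- **Sham group:** the sham electrode is a non-connected dummy of identical appearance. On the message given, this section says "The patient will be told that he/she is either in the group where he can feel the stimulation or in the group where the stimulation" (described there as sub-threshold). It calls patients blinded and doctors not.

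The Questionnaires section has study nurses complete the forms together with the patient and does not say whether the nurses are blinded. The Aim section makes the effect on the three scores the secondary endpoint.

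**The concern.** MFI20, BDI and SF-36 are subjective. A score serves as a baseline in a randomised comparison only if nothing that depends on the arm could have influenced it. If the visit runs as written, the patient may know before answering whether the stimulation is to be felt or not, and hope or disappointment could then move the answers differently in the two arms.

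What is at stake is the between-arm comparison of the questionnaire scores. The Discussion (Endpoints) also expects the study to show which questionnaires are most sensitive to taVNS in this population, and lists sample size among the information for a later trial. A distorted baseline would weaken the first use, and the second wherever it draws on these scores.

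**Working it through.** No figure in the plan is in dispute, so the check has two parts.

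**1. Can arm-dependent information reach the patient before baseline?**

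- *Order.* Visit 0 lists hand-over and instruction before the questionnaires. No other section shown reverses this.
- *Hand-over implies allocation.* The electrode is either working or a dummy, so a complete device cannot be given out before the arm is known to staff.
- *Instruction carries a message.* The Patients section ties the sub-threshold message for sham patients to the instruction in device use. If the instruction precedes the questionnaires, so can the message. The Sham group section words the message neutrally (one group or the other). Under that wording the patient learns which group only on trying the device.
- *Sensation.* Setting the intensity produces tingling in the active arm only. The text does not say whether this is done at Visit 0 before the questionnaires.

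The route through the spoken message therefore needs only the narrated order and the Patients wording. The route through sensation also needs the device to be switched on first.

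**2. What would a shift do?**

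Inputs: 15 per arm (Justification of sample size). Assumed: a between-arm baseline shift *b* of 0.1 to 0.3 SD, a baseline-to-follow-up correlation *r* of 0.3 to 0.7, and equal SDs at both times. Neither *b* nor *r* is given in the documents. Bias is measured against what a baseline taken before allocation would have given.

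- Standard error of a two-arm difference, in SD units: √(2/15) = 0.365.
- **4-week scores alone:** bias 0. Half-width 2.048 × 0.365 = 0.748 SD.
- **Change scores:** bias of size *b*, i.e. 0.1 to 0.3 SD. Half-width 0.748 × √(2(1 − r)):
  - r = 0.3: 0.885
  - r = 0.5: 0.748
  - r = 0.7: 0.579
- **Baseline-adjusted (ANCOVA):** bias of size *r·b*, from 0.3 × 0.1 = 0.03 to 0.7 × 0.3 = 0.21 SD. Half-width 2.052 × 0.365 × √(1 − r²):
  - r = 0.3: 0.715
  - r = 0.5: 0.649
  - r = 0.7: 0.535

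Bias as a share of the half-width:

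- Change scores: 0.1/0.885 = 11% to 0.3/0.579 = 52%. At r = 0.5 it is 0.1/0.748 = 13% to 0.3/0.748 = 40%.
- ANCOVA: 0.03/0.715 = 4% to 0.21/0.535 = 39%.

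A shift of 0.1 to 0.3 SD is smaller than one standard error of the chance baseline difference (0.365 SD), so the data could not separate it from ordinary imbalance.

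**The case against.** The strongest reply is that sentence order is weak evidence of visit order. The one sequencing word joins consent to hand-over. The questionnaires stand in a separate paragraph with no such link, and the device paragraph is not strictly chronological, since it also covers daily logging and the read-out at the end of the study. Table 1, which the Methods section says sets out when interventions and questionnaires take place, is not shown, and a condensed article may leave the steps of a visit to the full protocol. This stands as a limit on certainty. It does not remove the point: the article does give an order, it is the unfavourable one, and the Visit 0 text would need correcting even if Table 1 or the full protocol said otherwise.

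A reader might infer that patients have tried the device by then and that the baseline already carries knowledge of the arm. The documents do not support that. They do not say when in the visit randomisation occurs, or that the device is switched on before the forms are completed. Patients could at most learn felt versus below threshold, not active versus sham, and the Patients section itself allows that sub-threshold stimulation could in theory work. What remains is that felt versus below threshold still follows the arms and can still shape expectation.

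A reader might also infer that any shift passes one-for-one into the result, or that baseline adjustment becomes invalid. The Statistical analysis section names a difference in means or a Hodges-Lehmann difference. It names neither change scores nor adjustment, so the consequence depends on an analysis choice that the article leaves open.

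**Conclusion.** The point holds as an unfixed and unfavourably narrated sequence. Followed as written, Visit 0 allows the three self-reported baselines to be taken after arm-dependent information has reached the patient, and no text shown prevents it. That the baseline is in fact contaminated is not established.

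The bias would be the whole shift for change scores, *r* times the shift for a baseline-adjusted comparison, and none for a comparison of 4-week scores alone. The actual shift is unknown, and the shares of the half-width given above rest on assumed values of *b* and *r*. The primary endpoint, mean daily stimulation time, has no baseline and is unaffected. The change is worth making because it removes this source of bias at baseline for almost nothing, in a study where the bias could not be detected afterwards.

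**What to change.** State the order of Visit 0 explicitly:

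1. Informed consent.
2. MFI20, BDI and SF-36 completed and saved in REDCap.
3. Randomisation released.
4. Device hand-over, instruction and app pairing.

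Make the REDCap randomisation conditional on the three saved baseline forms. Because allocation would not yet exist when the nurses complete the forms with the patient, this also removes any influence of staff knowledge at baseline. If the visit already runs this way, correct the Visit 0 text to say so and check that Table 1 agrees.

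The cost is a reordered paragraph and one form dependency in REDCap. Sample size, number of visits and treatment do not change.

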### 4-week-stimulation phase

#### Visit 1

After 4 weeks, the patient has a new appointment at the outpatient clinic of the Neurosurgical Department. The questionnaires are filled out, and the stimulation statistics are read from the smartphone app, under the patient’s supervision. The patient’s weight is measured again. If a patient is unable to physically appear to the second visit, he/she will be given a temporary patient’s access to the respective REDCap® eCRF to fill out the missing questionnaires. The stimulator is given back to the hospital.

### Justification of sample size

Acceptance and compliance are considered successful when at least 80% of patients fulfills the acceptance criteria as defined in the primary endpoint. A total of 30 patients will be recruited, 15 in each of the two groups “sham” and “stimulation.” The sample size of 15 subjects per group was based on feasibility, as taVNS against cancer-related fatigue has not been investigated before. It is also based on studies investigating non-invasive VNS against sleep deprivation [45], lupus [46], and Sjoegren syndrome [47]. The choosen sample size adheres to the recommendations of sample sizes in feasibility studies [48, 49]. We will probably see a power of approximately 80% to detect if less than 50% of the patients fulfills the acceptance criteria with an exact one-sided binomial test at significance level 5%. Furthermore, with this sample size, the expected length of the 95% confidence interval for the adherence rate within one group lies between 0.38 and 0.44 and between 0.28 and 0.33 for the pooled rate. The expected length was calculated using the Agresti-Coull method and assuming a true rate between 50 and 80%.

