### Statistical analysis

For the descriptive analyses of the primary endpoint and all binary secondary endpoints absolute numbers, percentages and 95% confidence interval (CI) using Agresti-Coull method will be calculated. For comparisons between groups, odds ratio and corresponding 95% CI will be calculated. For continuous secondary endpoints mean, standard deviation and the 95% CI for the mean or median and quartiles will be calculated. For comparisons, difference between means and corresponding 95% CI or difference in location parameters using the Hodge-Lehman method and corresponding 95% CI will be determined. Furthermore, for the primary endpoint, we will test the null hypothesis “acceptance rate is higher than 80%” with an exact one-sided binomial test with significance level 5%.

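### The stated power of about 80% does not belong to the named exact test: it is 69.6% with 15 patients and 95.1% with 30

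*Protocol article*

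**What the plan says.** Under Justification of sample size, the protocol article sets the numbers: "A total of 30 patients will be recruited, 15 in each of the two groups “sham” and “stimulation". It then states: "We will probably see a power of approximately 80% to detect if less than 50% of the patients fulfills the acceptance criteria", and names the method: "with an exact one-sided binomial test at significance level 5" per cent. No sample is attached to the power figure. The next sentence gives expected confidence interval lengths for both candidates: "for the adherence rate within one group lies between 0.38 and 0.44 and between 0.28 and 0.33 for the pooled rate".

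The null hypothesis appears only under Statistical analysis: "we will test the null hypothesis “acceptance rate is higher than 80%” with an exact one-sided binomial test with significance level 5" per cent. The test therefore rejects when the number of accepting patients is low, and the power in question is the probability of rejecting 80% when the true rate is 50% or less.

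**The concern.** Once the sample size, null value, alternative and level are fixed, the power of an exact binomial test is a single number. All of these are stated except which of the two samples applies, so the figure can be checked directly. With samples this small, the binomial distribution moves in large steps and the exact test can use much less than its nominal 5%. A round power of about 80% is then easily off.

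This is the only power statement in the article, and it concerns the primary endpoint. The null hypothesis is that the treatment is accepted, so a non-significant result is likely to be read as support for acceptance. Power is then the main protection against calling the treatment acceptable when only about half of the patients use it enough. The Discussion (Endpoints) says that the results will inform a later randomised trial, including adherence and sample size.

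**Working it through.** **Inputs**

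- Test: exact one-sided binomial, nominal level 0.05 (Justification of sample size; Statistical analysis).
- Null boundary: p0 = 0.80, rejected on low counts (Statistical analysis).
- Alternative: p1 = 0.50, the boundary of the range below 50% (Justification of sample size).
- Sample: n = 15 (one group) or n = 30 (both groups pooled).

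**Which samples are meant.** The Agresti-Coull expected lengths for true rates between 50% and 80% recompute to 0.387–0.442 for n = 15 and 0.281–0.332 for n = 30. These match the printed 0.38–0.44 and 0.28–0.33 apart from rounding, so 15 and 30 are the right candidates.

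**Attempt to reproduce 80% with the named test.** Take the largest c with P(X ≤ c | n, 0.80) ≤ 0.05. The power is P(X ≤ c | n, 0.50).

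- n = 15: P(X ≤ 8 | 0.80) = 0.0181 and P(X ≤ 9 | 0.80) = 0.0611, so c = 8. Power = P(X ≤ 8 | 0.50) = 0.5 + 6435/32768 = 0.6964.
- n = 30: P(X ≤ 19 | 0.80) = 0.0256 and P(X ≤ 20 | 0.80) = 0.0611, so c = 19. Power = P(X ≤ 19 | 0.50) = 0.9506.

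| Sample | Reject if accepters | Actual level | Power at 50% | Type II error | Difference from 80% |
|---|---|---|---|---|---|
| 15 | ≤ 8 | 1.8% | 69.6% | 30.4% | −10.4 points |
| 30 | ≤ 19 | 2.6% | 95.1% | 4.9% | +15.1 points |

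The 80% is not reproduced.

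**Other readings of the exact test**

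- Reversed hypotheses (null 50%, true rate 80%): for n = 15, P(X ≥ 12 | 0.80) = 64.8%; for n = 30, P(X ≥ 20 | 0.80) = 97.4%.
- Two-sided exact test, 80% against 50%: 69.6% and 95.1%.
- One-sided level of 10%: 84.9% and 97.9%.

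**Where a figure near 80% does arise**

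- Normal approximation, n = 15, null 0.50 and alternative 0.80: z = (0.30 − 1.645·√(0.25/15)) / √(0.16/15) = (0.30 − 0.2124)/0.1033 = 0.848, which gives 80.2%.
- Arcsine approximation, n = 15: 80.2%.
- Normal approximation, n = 15, in the direction the article states (null 0.80, alternative 0.50): 84.3%.
- Randomised version of the exact test, n = 15: 81.0%.
- Ordinary exact test with n = 14, which is not a planned sample: 78.8%.

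The printed 80% is therefore probably a large-sample figure for one group of 15. That is an inference, since the article names the exact test.

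**True rates below 50%, n = 15 (reject at ≤ 8)**

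| True rate | 50% | 49% | 48% | 47% | 46% | 45% | 40% |
|---|---|---|---|---|---|---|---|
| Power | 69.6% | 72.3% | 74.9% | 77.3% | 79.7% | 81.8% | 90.5% |

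**The case against.** Four points can be made for the article. First, the number of patients was chosen for feasibility, with reference to earlier stimulation studies and to recommendations for feasibility trials. It is also supported by interval lengths that recompute correctly, so N was not derived from the power figure. Second, the sentence is hedged and speaks of rates below 50%, not of exactly 50%; with 15 patients the power reaches about 80% a few points lower, near 46%. Third, for the pooled 30 patients the statement understates the power, which is the cautious direction. Fourth, the figure has a plausible source in a standard approximation.

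The first point stands: nothing here calls for more patients or a different threshold. The second does not rescue the figure. A power claim for a range of alternatives has to hold at the end nearest the null, where power is lowest, and a gap of 10 to 15 points is more than the word approximately can cover. The third only shows that the error changes sign with the sample, which the sentence does not name. The fourth explains the figure but leaves it wrong for the exact test the article names.

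**Conclusion.** The stated power is wrong for the test as described. At a true acceptance rate of 50% the exact one-sided 5% test has 69.6% power with 15 patients and 95.1% with 30. The two candidates differ by about 25 points, so a reader cannot interpret the sentence without knowing which sample is used. For one group of 15, the chance of missing a 50% acceptance rate is 30.4% instead of 20%.

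The result rests on the article's own inputs (null boundary 80%, alternative 50%, one-sided 5%, full recruitment) and on judging power at the 50% boundary. It does not depend on the direction of the hypotheses, because the reversed exact test also misses 80% at both sample sizes.

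**What to change.** Decide whether the primary test uses one group (and which) or the pooled sample, and replace the power sentence with the matching statement:

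- One group of 15: the exact test rejects at 8 or fewer accepters (actual level 1.8%) and has 70% power if the true rate is 50%; power reaches about 80% at a true rate of about 46%.
- Pooled sample of 30: the exact test rejects at 19 or fewer accepters (actual level 2.6%) and has 95% power if the true rate is 50%.

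If both analyses are kept, give both lines and say which one decides. If the large-sample figure is retained for any reason, label it as an approximation and print the exact value beside it.

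The cost is one sentence and no extra patients. The only loss is that the single-group figure looks less favourable than the one now printed.

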### Statistical analysis

For the descriptive analyses of the primary endpoint and all binary secondary endpoints absolute numbers, percentages and 95% confidence interval (CI) using Agresti-Coull method will be calculated. For comparisons between groups, odds ratio and corresponding 95% CI will be calculated. For continuous secondary endpoints mean, standard deviation and the 95% CI for the mean or median and quartiles will be calculated. For comparisons, difference between means and corresponding 95% CI or difference in location parameters using the Hodge-Lehman method and corresponding 95% CI will be determined. Furthermore, for the primary endpoint, we will test the null hypothesis “acceptance rate is higher than 80%” with an exact one-sided binomial test with significance level 5%.

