### Aim

It is the aim of the study to investigate whether 4 h of daily taVNS is accepted as a treatment against CRF and whether the symptoms of CRF and QoL can be influenced by taVNS in patients with gastrointestinal tumors and clinically apparent CRF.Primary endpoint: Acceptance of and compliance to taVNS, measured with the mean duration of taVNS per day. taVNS, is considered accepted when at least 80% of patients use the stimulator an average of at least 2 h per day.Secondary endpoint: Effect of taVNS on clinical scores (MFI20, BDI, and SF-36)

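### Acceptance is compared between arms of 15 by an odds ratio alone; a risk difference should be added, because the odds ratio breaks down if an arm is full (minor)

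*Protocol article*

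**What the plan says.** The Statistical analysis section of the protocol article treats the primary endpoint and the binary secondary endpoints together. Within arms, "absolute numbers, percentages and 95% confidence interval (CI) using Agresti-Coull method will be calculated". Between arms, "For comparisons between groups, odds ratio and corresponding 95% CI will be calculated". No other between-arm measure is named for binary endpoints. For continuous endpoints the same section uses differences, either of means or of location by the Hodges-Lehmann method.

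The secondary endpoints listed under Aim are questionnaire scores, so in practice the odds-ratio sentence governs acceptance.

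Arm size is fixed under Justification of sample size: "A total of 30 patients will be recruited, 15 in each of the two groups". Under Aim, treatment "is considered accepted when at least 80% of patients use the stimulator an average of at least 2 h per day". The precision calculation was made "assuming a true rate between 50 and 80" percent.

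**The concern.** An odds ratio needs at least one acceptor and one non-acceptor in each arm. With 15 patients per arm and a success threshold of 80%, an arm at the threshold has only three non-acceptors, and a better arm may have none. The single named contrast then has no finite value. Even short of that, one or two patients drive it.

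What is at stake is the description of how far acceptance differs between stimulation and sham. The question is reasonable here, since sham patients feel nothing from their electrode. The Discussion (Endpoints) also says the findings on adherence are meant to inform a later randomised trial. A planner would want that difference in percentage points with an interval.

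**Working it through.** **Inputs.** n = 15 per arm and a planning range for the true rate of 50–80% (Justification of sample size); success threshold 80% (Aim); odds ratio as the contrast (Statistical analysis). True rates of 85% and 90% are my assumptions. The protocol does not state them.

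**Plan's own figures.** The document gives no figure for the odds ratio. The expected Agresti-Coull interval lengths do reproduce: 0.385 to 0.442 per arm (stated 0.38 to 0.44) and 0.280 to 0.332 pooled (stated 0.28 to 0.33). This confirms the arm size and the planning range. The power statement in the same section concerns the single-rate test and plays no part here.

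**Step 1: chance of a full arm.** With independent patients and the same true rate p in both arms, P(at least one arm 15/15) = 1 - (1 - p^15)^2.

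| True rate p | p^15 | At least one full arm | Both full |
|---|---|---|---|
| 50% | <0.0001 | about 0.01% | about 0 |
| 70% | 0.0047 | 0.95% | about 0 |
| 80% | 0.0352 | 6.9% | 0.1% |
| 85% (assumed) | 0.0874 | 16.7% | 0.8% |
| 90% (assumed) | 0.2059 | 36.9% | 4.2% |

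With 80% in one arm and 90% in the other (also assumed): 1 - (1 - 0.0352)(1 - 0.2059) = 23.4%.

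**Step 2: the odds ratio at 15/15 v 12/15.**
- Sample value: (15 × 3)/(0 × 12), which is infinite. The Wald standard error contains 1/0, so there is no finite interval.
- Exact conditional interval: given 27 acceptors in total, the lower limit ψ solves 455ψ³/(455 + 1575ψ + 1575ψ² + 455ψ³) = 0.025, so ψ = 0.43. The upper limit is infinite.
- Adding 0.5 to each cell: (15.5 × 3.5)/(0.5 × 12.5) = 8.68. The standard error of the log is √(1/15.5 + 1/0.5 + 1/12.5 + 1/3.5) = 1.559, so the 95% CI is 0.41 to 184.
- With 15/15 in both arms, the sample odds ratio is 0/0.

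**Step 3: the risk difference for the same data.** The Wilson limits are 0.796 to 1 for 15/15 and 0.548 to 0.930 for 12/15. Newcombe's method combines them:
- lower: 0.20 - √((1 - 0.796)² + (0.930 - 0.80)²) = -0.04
- upper: 0.20 + √((1 - 1)² + (0.80 - 0.548)²) = 0.45

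The result is 20 points (-4 to 45). With both arms full it is 0 points (-20 to 20).

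**Step 4: no empty cell, 14/15 v 12/15.** The odds ratio is (14 × 3)/(1 × 12) = 3.5. The standard error of the log is √(1/14 + 1/1 + 1/12 + 1/3) = 1.220, so the 95% CI is 0.32 to 38. The risk difference is 13 points (Newcombe -13 to 39).

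**The case against.** **The odds ratio can still be reported.** The article names no interval method, and an exact or corrected version exists when one arm is full. This stands. A reader might infer that the contrast cannot be estimated at all. That is true only of the ordinary odds ratio with a Wald interval, or when both arms are full. The interval method and the handling of empty cells are commonly left to the SAP, which is not shown, so their absence is no defect. What remains is that the exact and corrected versions carry almost no information at this size.

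**80% is a threshold and not a forecast.** This also stands. A reader might infer that the trial expects acceptance of 80% or more and that a full arm is therefore likely. The only range assumed in planning is 50–80%, where the chance is at most 6.9%. The Discussion is cautious too: it reports high drop-out with an earlier device and says that patients with fatigue are hard to motivate. On the other side, a trial with a true rate of exactly 80% would observe at least 24/30 acceptors only 61% of the time, against 85% and 97% at true rates of 85% and 90%. Rates above the threshold therefore fit a trial that succeeds reliably, but they remain assumptions.

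**Little is lost.** Counts, percentages and per-arm intervals are reported anyway, so 100% against 80% would be visible and the difference follows by subtraction. This stands, except that subtraction gives no interval for the difference. The Discussion's list of what the next trial needs includes adherence but does not name a between-arm difference in it.

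**Width comes from n = 15, whatever the scale.** This is largely right. The risk-difference interval spans about 49 points for 15/15 v 12/15 and 52 points for 14/15 v 12/15. Its advantage is that it stays finite and is in percentage points. That supports adding it, but does not make removal of the odds ratio necessary.

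**Conclusion.** The point holds as a minor one, worth considering. The only between-arm measure named for acceptance has no finite sample value when exactly one arm of 15 is full and is undefined when both are. The chance of at least one full arm is at most 6.9% within the planning range, and 17% and 37% at assumed rates of 85% and 90%. These figures rest on independent patients, 15 analysed per arm and equal true rates in the two arms.

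A reader might infer that the primary result would be lost in the favourable scenario. The document does not support this: success is judged on the acceptance rate, "we will test the null hypothesis “acceptance rate is higher than 80%” with an exact one-sided binomial test with significance level 5" percent is a test of that rate, and the Agresti-Coull intervals per arm are untouched. The effect is confined to the descriptive contrast between stimulation and sham.

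**What to change.** In the Statistical analysis section, add the risk difference (stimulation minus sham) with a Newcombe (Wilson score) 95% CI as the main between-arm contrast for acceptance and any other binary endpoint, and keep the odds ratio as supplementary. This also brings binary endpoints into line with the differences already planned for continuous ones.

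The cost is one sentence and one more reported measure. It needs no new data or patients and no change to the primary test.
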